### Randomization

Participants will be randomly assigned to 1 of 4 conditions in a 2 (social support groups: yes or no) × 2 (SBCM: yes or no) between-participants factorial design. Randomization will occur on an individual basis using the REDCap (Research Electronic Data Capture; Vanderbilt University) randomization module. An equal number of participants will be randomly assigned to each condition. Randomization will occur in blocks of 8 and be stratified based on sex. Neither participants nor study staff will be blinded to condition assignment.

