#### SBCM Intervention

This adapted individually tailored SBCM intervention [21] is delivered by telephone or video by trained research staff over 5 sessions. The first session lasts 45 to 60 minutes and is focused on the following: (1) developing facilitator-participant rapport; (2) discussing participants’ background, current needs, and life challenges (eg, transportation, food insecurity, insurance, mental health, or technology); (3) identifying and ranking life challenges that participants experience as stressors and barriers to HIV care or quality of life; (4) identifying 1 stressor to focus on for the remaining sessions; (5) discussing past strategies to deal with the stressor; and (6) setting a short-term goal related to the stressor. After the first session, the facilitator compiles and sends the participant relevant, individually tailored resources (local and online) to aid in addressing contextual factors related to the stressor of focus. During the second session of similar length, the facilitator and participant will (1) review the resource list; (2) assess progress toward the short-term goal; (3) talk about accomplishments, strengths, and skills the participant has identified in their own life; and (4) revise the strategy to achieve the participant’s goals, incorporating identified strengths and skills to support progress. The final 3 sessions are optional, brief (15-30 min) check-ins, occurring at 1- to 2-week intervals, as determined by the participant and facilitator. These sessions focus on the achievement of an intermediate or long-term goal via the same collaborative process carried out in the first 2 sessions.

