### Procedures

Participants will be screened for eligibility using a web-based screener or by telephone. Study flyers contain the study web page, QR code, and our study telephone number. Online advertisements and postings contain a direct link to the screener. Study staff will contact eligible participants by telephone to describe the study, review the main components of the consent, and answer questions. Participants interested in enrolling will be sent either (1) a link to the web-based informed consent document and baseline survey by email or SMS text message or (2) a packet containing the informed consent document, baseline survey, and a stamped and addressed envelope for survey return via US mail. All participants interested in enrolling will also be sent a DBS study kit via US mail (refer to the HIV Viral Load Testing subsection). To guard against duplicate and fraudulent enrollments, we will require a unique and valid telephone number and postal address for each participant and speak with each participant before enrollment.

Only eligible participants who enroll in the study, complete a baseline survey, and return the baseline DBS study kit to the laboratory will be randomly assigned (refer to the Randomization subsection). After assignment, participants will be offered 0, 1, or 2 remote interventions depending on group (refer to the Interventions subsection). These interventions will be delivered over 5 to 8 weeks. Participants will complete follow-up assessments at 4, 8, and 12 months after assignment and provide DBS specimens at 4 and 12 months after assignment.

We will maximize retention by collecting multiple types of contact information (eg, telephone numbers, email address, and postal address) from participants upon enrollment. We will maximize participation in intervention sessions by providing reminders before each session using each participant’s preferred method of communication and by providing a modest compensation for each core intervention session attended.

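### A single, published block size of 8 within sex, in an open-label trial, leaves up to about 14% of exact conditions and 20% of each intervention's yes/no assignments deducible by staff who track allocations

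*Protocol article*

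**What the plan says.** The Randomization section of the protocol article fixes the mechanism. Assignment is to one of four conditions in the 2×2 factorial, and "An equal number of participants will be randomly assigned to each condition". On how it is done: "Randomization will occur on an individual basis using the REDCap (Research Electronic Data Capture; Vanderbilt University) randomization module". On restriction: "Randomization will occur in blocks of 8 and be stratified based on sex". On masking: "Neither participants nor study staff will be blinded to condition assignment".

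Three other sections bear on how knowledge of allocation could be used.

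- **Procedures:** "Study staff will contact eligible participants by telephone to describe the study, review the main components of the consent, and answer questions". Assignment follows only once the person has enrolled, completed the baseline survey and returned the baseline dried blood spot (DBS) kit to the laboratory.
- **SBCM Intervention:** strengths-based case management (SBCM) "is delivered by telephone or video by trained research staff over 5 sessions". The support groups are run by facilitators from the partner organization.
- **Results:** 177 people had consented by July 2025, and recruitment is planned to finish by April 2026.

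**The concern.** With one block size and four equal conditions, every block of 8 holds exactly two places per condition, and so four yes and four no places for each intervention. As a block fills, the remaining places can be worked out from those already used. There are no site strata, so the whole trial runs on two lists, one per sex. Staff are not blinded, and the block size is now in print while people are still being enrolled. Keeping the table inside REDCap hides the table. It does not stop someone from subtracting past assignments from a known total.

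The risk is selection before assignment. Staff speak to candidates before consent and could, knowingly or not, pursue one person harder or change the order in which ready people are randomized. Three of the four primary outcomes (adherence, quality of life, depressive symptoms) are self-reported and plausibly related to baseline need. Steering by need would therefore bias the comparison.

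**Working it through.** **Inputs.** Four conditions, equal allocation, block size 8 and strata by sex only (Randomization); N = 352 (Sample Size); 177 consented by July 2025 (Results). The article gives no figure for predictability. Its power statement is not affected: 352 × 0.80 / 2 = 140.8 per level gives power 0.84 for 0.35 SD at two-sided 0.05 (two-sided is assumed), which agrees with the stated 0.80 or greater.

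**Observer assumed.** The observer knows the block size, the block boundaries and every earlier assignment in the stratum. All results below are therefore upper bounds.

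**Yes/no status for one intervention (4 yes, 4 no per block).** The last k places are all of one kind with probability 2·C(8−k, 4)/C(8, 4), where C(8, 4) = 70:

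- k = 1: 2 × 35/70 = 1
- k = 2: 2 × 15/70 = 0.429
- k = 3: 2 × 5/70 = 0.143
- k = 4: 2 × 1/70 = 0.029

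The sum is 1.6 assignments per block, and 1.6/8 = 20.0%. By symmetry the figure is the same for the support groups and for SBCM.

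**Exact condition (2 places for each of 4).** The 8th place is always determined. The 7th is determined when the last two places are the same condition, with probability 4/C(8, 2) = 4/28 = 1/7. The sum is 1 + 1/7 = 1.143, and 1.143/8 = 14.3%.

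**By position in the block:**

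| Position | Exact condition certain | Yes/no certain | Best guess correct, yes/no |
|---|---|---|---|
| 1 | 0% | 0% | 50.0% |
| 2 | 0% | 0% | 57.1% |
| 3 | 0% | 0% | 57.1% |
| 4 | 0% | 0% | 62.9% |
| 5 | 0% | 2.9% | 62.9% |
| 6 | 0% | 14.3% | 71.4% |
| 7 | 14.3% | 42.9% | 71.4% |
| 8 | 100% | 100% | 100% |

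Averaged over the block, the best guess is right 66.6% of the time for yes/no (chance 50%) and 47.0% for the exact condition (chance 25%).

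**Scale.** Over the whole trial, 352/8 = 44 blocks, so 44 × 1.6 ≈ 70 yes/no statuses per intervention and 44 × 1.143 ≈ 50 exact conditions. Only people not yet assigned can be protected: 352 − 177 = 175, so 175 × 0.20 = 35 yes/no statuses per intervention and 175 × 0.143 ≈ 25 exact conditions. Consent precedes randomization, so the number still to be assigned in July 2025 may have been somewhat above 175.

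**Effect of varying the block size.** This was simulated with an observer who knows the set of possible sizes but not which one is in use. The sizes and a stratum of 264 (75% of 352) are assumptions.

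| Block sizes | Exact certain | Yes/no certain | Best guess, exact | Best guess, yes/no |
|---|---|---|---|---|
| 8 only | 14.3% | 20.0% | 47.0% | 66.6% |
| 4, 8, 12 | 3.8% | 5.3% | 46.2% | 66.0% |
| 8, 12, 16 | 2.3% | 3.3% | 43.6% | 63.9% |

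Varying the size removes most of the certainty and little of the informed guessing.

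**The case against.** The strongest reply is that the article describes real safeguards. Assignments come from the REDCap module, one person at a time, after consent, baseline survey and DBS return. Nothing says that staff can see the upcoming list. A reader might infer that allocation is not concealed at all; the documents do not support that. Even the fully informed observer is uncertain of at least 80% of assignments on either scale.

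A reader might also infer that a single team enrols participants and delivers SBCM. The article says only that research staff deliver SBCM. It does not say that they also enrol, and the partner organization runs the groups. Nor does it say that enrolling staff follow both lists or know where blocks begin. Access rights and who generates the table are commonly left to the full protocol, so silence on them is not held against this article.

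The scope for steering is limited. Participants collect and post their own samples, the laboratory logs arrival, and staff help when called. Much of the timing therefore lies with the participant and the post. What remains is mainly whom staff pursue and the order in which ready people are randomized.

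Finally, it would be too strong to say that such selection could never be detected or adjusted for. The Statistical Analysis section compares baseline demographics and outcomes across conditions and adjusts for differences, and several markers of need are measured before assignment. Steering on unmeasured traits, or steering too slight to reach significance, would escape this.

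All these points narrow the concern. None removes it, because the single block size, the two lists, the unblinded staff and the publication during enrolment are all stated.

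**Conclusion.** The point holds as a partial, avoidable weakness in concealment. Up to 14.3% of exact conditions and 20.0% of each intervention's yes/no assignments can be known in advance. For those still to be enrolled in July 2025 that is at most about 35 of roughly 175 participants per intervention. The figure of about 70 over all 352 is arithmetically right, but it should not be read as expected exposure: it is an upper bound and includes people already enrolled.

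The conclusion assumes that blocks of 8 means a constant size, which is the natural reading. It also assumes an observer who knows the size, the boundaries and all earlier assignments in the stratum. No passage shows that anyone has used such knowledge, and the article does not establish that bias has occurred.

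**What to change.** For participants not yet randomized, load a REDCap allocation table with randomly varying block sizes, in multiples of 4, within sex. Sizes 8, 12 and 16 are preferable to a set that includes 4, since a block of 4 is itself the most predictable (25% of exact conditions and 33% of yes/no assignments certain). Have the table generated by someone who does not enrol participants, and withhold the sizes from staff until enrolment ends. In the Randomization section, replace the fixed block size with a statement that sizes vary at random, and give the date of the change. Do not publish the sizes while enrolment is open.

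The benefit is that yes/no assignments known with certainty fall from 20.0% to about 3.3%, and exact conditions from 14.3% to about 2.3%. With 4, 8 and 12 the figures would be 5.3% and 3.8%. Best-guess accuracy for yes/no falls only from 66.6% to about 64%, and this should be stated plainly.

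The cost is one new table and one amended sentence. An incomplete final block may leave a small imbalance: in a block of 16, with four places per condition, two conditions can differ by at most 4 per stratum, against 2 in a block of 8. A block of 8 left open at the changeover could add up to 2 per stratum. The sample size and power statement need no change.

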## Methods

### Overview of Study Design

This RCT will assess the efficacy of 2 remotely delivered interventions—supportive-expressive peer social support groups and individual SBCM—for increasing viral suppression, ART adherence, and health-related quality of life, as well as decreasing depressive symptoms, among 352 rural older people living with HIV in the southern United States. We will assess these 2 interventions using a 2×2 factorial design. Interventions will be delivered over a 5- to 8-week period, and participants will complete surveys at baseline and 4-, 8-, and 12-month follow-ups and viral load assessments at baseline and 4 and 12 months. Participant flow through the study is shown in Figure 1. The study is being conducted by researchers at the Medical College of Wisconsin’s Center for AIDS Intervention Research and community partners at the Southern AIDS Coalition.

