#### Supportive-Expressive Peer Social Support Groups Intervention

This program, adapted from Project Linkage [25], is delivered to groups of approximately 8 to 12 participants by trained facilitators from the Southern AIDS Coalition. The groups meet weekly for 90-minute sessions over 8 weeks. Participants may choose to join each session by videoconference with or without video, or they may join by telephone for an audio-only experience. Each session has a unique focus: (1) introductions, program overview, and establishing group rules and expectations; (2) feelings around HIV diagnosis, stigma, and questions of “why did HIV happen to me?”; (3) values and priorities in life and thoughts about mortality; (4) uncertainty, challenges, and lack of control; (5) physician-patient relationship; (6) friend and family relationships; (7) body image and sense of self; and (8) reflection, summary, and closure. On the basis of participant feedback during our pilot, we incorporated the topic of HIV-related stigma into this intervention and also recruited group facilitators who had more shared lived experiences with participants. After the 8 group meetings, participants in groups are offered the opportunity to share their contact information with other participants if they are interested and sent instructions on how to host their own videoconference meetings should they wish to continue meeting to provide mutual social support.

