**Covariates (baseline)**			
	Demographics, socioeconomic position, and health	Age, sex, gender identity, sexual orientation, race and ethnicity, education, income, employment, insurance status, years living with HIV, number of comorbid health conditions, and mode of survey completion (web-based vs paper)	
	Geography	State of residence and Index of Relative Rurality [38,49]	
	Use of other services	Use of HIV case management and participation in other social support groups	

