### HIV Viral Load Testing

At enrollment, 4 months, and 12 months, participants will be sent a DBS kit by US Postal Service to self-collect a blood sample for HIV viral load testing. The DBS kits contain a HemaSpot collection device (volume capacity 80 μL); alcohol pads; 2 single-use retractable safety lancets; gauze pads; bandages; a biohazard bag labeled with participant ID; a postage-paid envelope for specimen return; and an instruwction card, written at an eighth-grade reading level, that describes how to collect the specimen. Participants are instructed to call study staff if they need additional assistance while collecting their samples. Participants will return specimens directly to the clinical laboratory for testing using a preaddressed shipping envelope. Shipping will be tracked by the study team, and specimen arrival will be logged by the laboratory.

HemaSpot devices with sufficient blood volume will be tested using the automated Abbott m2000 platform and the RealTime HIV-1 DBS reverse transcription polymerase chain reaction assay [53]. The assay has a limit of detection (LOD) of 2.92 log copies/mL (839 copies/mL) and can quantify up to 7.0 log copies/mL [54]. When no HIV-1 RNA is detected, the laboratory will report a result of “not detected” or “undetectable.” Detectable specimens will be binarized into qualitative and quantitative results based on the LOD. Qualitative viral load results will include those detectable but not quantifiable, as they fall below the LOD of 839 copies/mL. The laboratory will report quantitative viral load results when HIV-1 RNA is both detectable and quantifiable (≥839 copies/mL). The primary outcome of viral suppression will be defined as a viral load of <839 copies/mL.

Self-collection of DBS specimens for viral load monitoring was shown to be highly feasible and acceptable in our pilot work with older rural people living with HIV [21].

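### The protocol leaves all study staff unblinded, although only participants and those delivering the interventions have to be; coded labels for the analyst and uniform follow-up contact would be a cheap gain

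*Protocol article*

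**What the plan says.** The protocol article (Randomization) settles blinding in one sentence: "Neither participants nor study staff will be blinded to condition assignment". It gives no reason and separates no roles.

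On delivery, SBCM "is delivered by telephone or video by trained research staff over 5 sessions" (SBCM Intervention). The support-group programme is "delivered to groups of approximately 8 to 12 participants by trained facilitators from the Southern AIDS Coalition" (Supportive-Expressive Peer Social Support Groups Intervention). Overview of Study Design names that coalition as a partner in conducting the study.

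On outcome data, surveys are filled in by the participant on the web or on paper (Ethical Considerations, Procedures). For viral load, "Participants will return specimens directly to the clinical laboratory for testing using a preaddressed shipping envelope", and the specimen is run on an automated platform with a cut-off of 839 copies/mL. The study team tracks shipping, and "Participants are instructed to call study staff if they need additional assistance while collecting their samples" (HIV Viral Load Testing).

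On analysis, Measures and Statistical Analysis let covariates into the outcome models when they are found to differ between conditions or to be related to retention.

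**The concern.** Masking is usually impossible for participants and facilitators in a trial of this kind, and the protocol is not at fault there. The blanket sentence goes further: on its face it also covers staff who deal with participants at follow-up, and any analyst counted as staff.

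Two things are at stake. First, the covariate set of the primary models depends on the data, and choices made in full view of condition labels and results can be questioned afterwards even when made in good faith. Second, surveys and blood spots are returned remotely and only 80% retention is expected, so staff help and contact can influence who supplies data. Three of the four primary outcomes (adherence, quality of life, depressive symptoms) are self-reported by participants who know their condition. Staff masking cannot remove that source of bias, which is a reason not to add an avoidable one.

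**Working it through.** **1. Where assessor judgement could enter.** Adherence, quality of life and depressive symptoms come from self-completed questionnaires. Viral suppression comes from a self-collected specimen bagged under a participant ID, sent straight to the laboratory and classified by a fixed threshold. No described outcome depends on a rater, so assessor bias is small.

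**2. Covariate choice in the primary models.** Statistical Analysis tests baseline demographics and outcomes across the four conditions and carries significant differences into the primary analyses. It also adds covariates associated with retention. Table 1 lists 16 covariate items. Sex is a stratification factor, which leaves 15. Adding the 4 primary and 7 secondary outcomes at baseline gives 15 + 4 + 7 = 26 candidates. If each is tested at 0.05 (an assumption, since no level is given for these tests), 26 × 0.05 = 1.3 would be expected to be flagged by chance alone. The covariate set is therefore likely to be altered by the data, and retention adds a second screen. All of this can be done with coded labels. The looser wording on covariates and on plotting interactions belongs to the exploratory moderation, dose, mode and mediation analyses and does not govern the primary models.

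**3. Staff contact.** Staff are described as doing the following:
- telephoning before enrolment, hence before randomization (Procedures);
- reminding participants of intervention sessions (Procedures);
- tracking specimen shipments and taking calls for help with collection (HIV Viral Load Testing).

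Only the last bears on outcome data after randomization. The article does not say whether the staff who take those calls, or who make any follow-up contact, also deliver SBCM.

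**4. The plan's own figure.** Inputs from Sample Size are 352 enrolled, 80% retained, 0.35 SD and alpha 0.05 (two-sided assumed).
- Per level of each factor: 352 × 0.80 / 2 = 140.8.
- Standard error of the difference: √(2/140.8) = 0.119 SD.
- Power: Φ(0.35/0.119 − 1.96) = 0.836.

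The stated power of 0.80 or greater reproduces for the continuous outcomes. Nothing proposed here changes it.

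**5. Illustration of size (assumed inputs only).** Suppose return differs by g percentage points between the two levels of a factor, centred on 80%, and the extra returners differ from the other returners by d = 0.5 SD. The shift in a raw comparison of returners is (g / higher return rate) × d.
- g = 5 (82.5% against 77.5%): (5/82.5) × 0.5 = 0.030 SD, which is 0.030/0.35 = 9% of the target.
- g = 10 (85% against 75%): (10/85) × 0.5 = 0.059 SD, which is 0.059/0.35 = 17% of the target, or about half a standard error (0.059/0.119).

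Neither g nor d has a source in the documents. The sign is also open: if the extra returners are harder-to-reach people who are doing worse, the shift works against the intervention. The planned mixed models, with retention-related covariates, would remove some part of it.

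**The case against.** The strongest case against the point has three parts.

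**The article is a condensed document.** Analyst masking and contact scripts are commonly left to the full protocol or analysis plan, and the article does not say whether the statistician counts as study staff. This stands as far as silence goes: the lack of a described masked analyst would be no finding by itself. It does not dispose of the Randomization sentence, which is a positive statement that staff are not blinded and makes no exception.

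**Differential retention is already handled in part.** Retention is compared across the four conditions, retention-related covariates enter repeated-measures models, and everyone is paid the same US $50 per survey and per specimen. This stands, and it reduces the stakes. It does not protect the covariate choice itself.

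**The asymmetry between interventions is not documented.** A reader might infer from SBCM's delivery by research staff that the same team runs outcome collection, so that the SBCM effect is biased and the support-group effect is not. The article does not support this. It never says that the same people do both. The partner that delivers the groups also conducts the study and helps with recruitment. Goodwill could arise in either factor: the groups offer 8 × 90 = 720 minutes of contact, while SBCM offers between 2 × 45 + 3 × 15 = 135 and 2 × 60 + 3 × 30 = 210 minutes one-to-one, the last three sessions being optional. Half of those not assigned to SBCM are offered the groups, and every participant speaks with staff before enrolment. This objection stands in full.

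**Conclusion.** The point holds in a narrow form. The protocol declines to blind any study staff, although only participants and interventionists must be unblinded. The avoidable exposure is data-dependent covariate choice in the primary models with conditions visible, together with unseparated staff help and contact around specimen return. That bias differs between the two interventions is a possibility the article leaves open, not something it states.

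The size cannot be derived from the documents. The 0.03 to 0.06 SD range rests wholly on an assumed 5- to 10-point return gap and an assumed 0.5 SD difference, with direction unknown, and it does not apply if return does not differ. This is a low-cost improvement and not a threat to the trial's validity.

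**What to change.** Amend the Randomization section to say that participants and those delivering the interventions are unblinded, and add two provisions.

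1. The analyst works with coded labels for each factor until the covariate set and primary models are locked and run. Session attendance, mode of delivery and intervention-satisfaction items reveal condition, so they stay out of the masked file. The dose, mode and acceptability analyses follow afterwards.
2. Contact about follow-up surveys and blood-spot kits, including help with collection, follows one script and schedule in all conditions. Where existing staffing allows, it is made by someone who did not deliver an intervention to that participant. The article should say whether staff who deliver SBCM currently make such contact.

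The cost is some relabelling work, minor scheduling inconvenience and later dose, mode and acceptability analyses. Sample size and power are unaffected. Results places the end of follow-up in April 2027 with analysis after that, so the coded labels can still be adopted in full and the contact rule for the follow-ups that remain.
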